### Vaccination history

Vaccination status of cohort members will be determined by a review of the PCCs' electronic clinical records, which contain specially designated fields for pneumococcal and influenza vaccinations. We assume that information in clinical records is complete, so a subject will be considered as unvaccinated when a vaccination was not recorded in the PCC clinical record.

Pneumococcal vaccination status (including number of dose of PPV-23 received in prior 10 years) will be determined at study start and it will be reevaluated at the end of the first and second year of the study period. Similarly, influenza vaccination status will be determined at the beginning of the study (according to reception or not of a dose of flu vaccine in prior autumn) and it will also be reevaluated every year of the study period.

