## Methods and Design

### Design, setting and study population

Population-based cohort study focused on adults over 60 years in the region of Tarragona, a mixed residential-industrial urban area in the Mediterranean coast of Catalonia, Spain.

Study subjects include 27,000 community-dwelling adults aged 60 years or more assigned to 9 participating Primary Care Centres (PCCs) in the study area, who will followed during a 30-month consecutive period. Six of the nine participating PCCs are located in Tarragona city (PCC Bonavista, PCC Torreforta, PCC Jaume I, PCC Sant Pere i Sant Pau, PCC Tarraco, PCC Sant Salvador) and three PCCs are located in nearby (less than 12 kilometres from Tarragona) smaller municipalities (PCC Salou, PCC Constanti and PCC Morell). Two reference hospitals for the study population are Hospital Joan XXIII and Hospital Santa Tecla, both located in Tarragona city (which has an overall population of approximately 120,000 all-age inhabitants).

It must be noted that, in Spain, primary care physicians are the first point of call for secondary and tertiary care and all citizens are registered in one PCC.

Inclusion criteria for the CAPAMIS cohort include: a) male or female adults aged 60 years or older as of January 1, 2009; and b) registered in any of the nine PCCs participating at study start. Exclusion criteria include residence in a long-term care facility. Subjects will be identified from primary care information systems. Figure 1 shows the study region and illustrates the location of participating centres.

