**Figure 1 F1:**
[figure not shown]
**Research areas of the CAPAMIS Study**. This figure illustrates the geographical distribution of the nine participating Primary Health Care Centers in the region of Tarragona (a mixed residential-industrial urban area, which is located 95 Km from Barcelona, in the mediterranean coast of Catalonia, Spain).

Cohort members will be followed from the beginning of the study (1 January 2009) until occurrence of the first event, the enrolment from the PCC ceases, death, or until the end of the study (30 June 2011).

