All cases of AMI and stroke will be further validated by checking hospital medical records with a standardized data-collection instrument that includes clinical characteristics of the events, and they will be classified as "CAP-related" (occurring within 30 days after onset of pneumonia) or "CAP-nonrelated" (ocurring more than 30 days after an episode of pneumonia or ocurring among patients who have not suffered a previous CAP).

Because of the size of the study, an active following of study participants is not feasible. Nevertheless, the nine PCCs and two reference hospitals provide daily care to the inhabitants living in the selected study area, and they basically apply similar diagnostic checklist and treatment for patients presenting with a clinical suspicion of pneumonia, myocardial infarction or cerebrovascular accident.

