### Covariates

Covariates will be age, sex, frequency of attendance (number of outpatient visits per year), history of pneumonia in 24-month before study start, history of coronary artery disease, history of prior stroke, presence of major cardiovascular risk factors (hypertension, hypercholesterolaemia, smoking, diabetes mellitus or obesity), presence of major comorbidities (chronic heart disease, chronic pulmonary disease, severe liver disease, chronic nephropathy or cancer) and immunological status. Table 2 lists covariates and shows criteria used to measure and capture underlying conditions and comorbidities in the study cohort.

**Table 2 T2:** Definitions and criteria used to collect respiratory and cardiovascular risk factors and main comorbidities among cohort members in the CAPAMIS Study.*

UNDERLYING CONDITIONS	DEFINITIONS
**History of prior pneumonia**	Includes influenza-related pneumonia (J10.0 and J11.0), viral pneumonia (J12), pneumococcal pneumonia (J13), pneumonia due to Haemophillus influenzae (J14), bacterial pneumonia (J15), pneumonia due to other infectious organisms (J16), pneumonia in diseases classified elsewhere (J17) and pneumonia due to unspecified microorganisms (J18).

**History of coronary artery disease**	Includes angina (I20), acute myocardial infarction (I21), subsequent or recurrent myocardial infarction (I22) and chronic ischaemic heart disease (I25).

**History of stroke**	Includes haemorrhagic stroke (I60 to I62), cerebral infarction (I63) and stroke not specified as haemorrhage or infarction (I64); it does not include transient ischaemic attacks (code G45).

**Hypertension**	Defined as the presence of any code I10, I11, I12, I13 or I15.

**Hypercholesterolemia**	Defined as the presence of code E78.

**Diabetes mellitus**	Codes E10 to E14.

**Obesity**	Patients with registered code E66 (BMI>30%).

**Smoking**	Includes patients with current smoking (code F17 active at study start).

**Alcoholism**	Includes patients with code F10 active at study start.

**History of heart disease**	Includes congestive heart failure (I50), hypertensive heart disease (I11), cardiomyopathy (I42), cardiac dilatation or ventricular hypertrophy (I11.9 or I51.7) and coronary artery disease (I20, I21, I22 and I25).

**History of vascular ischaemia**	Besides coronary artery disease and stroke, it Includes atheroesclerosis (I70), acute arterial embolism or thrombosis (I74) and peripheric arterial disease or intermittent claudication (I73.9).

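### Registration on one date plus a blank vaccination field defines the unvaccinated group, with no minimum registration or contact, so effectiveness is probably biased downward by an unknown amount

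*Protocol article*

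**What the plan says.** **Eligibility** (Design, setting and study population). Besides age, the only inclusion condition is being "registered in any of the nine PCCs participating at study start". The one exclusion named is long-term care: "Exclusion criteria include residence in a long-term care facility". Neither sets a minimum registration period or a prior contact.

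**Exposure** (Vaccination history). Status comes from the centre's electronic record: "We assume that information in clinical records is complete, so a subject will be considered as unvaccinated when a vaccination was not recorded". The history considered is long, "including number of dose of PPV-23 received in prior 10 years".

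**How doses are given** (Use of pneumococcal vaccine in the study area). The vaccine is offered free when patients attend primary care, in a programme across Catalonia with uptake of about 50%.

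**Follow-up** (text under Figure 1; Main outcomes and definitions). Person-time stops at the first event, the end of centre enrolment, death or 30 June 2011. Follow-up is passive: "Because of the size of the study, an active following of study participants is not feasible". The same paragraph adds that the nine centres and two reference hospitals serve the people living in the area.

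**Adjustment** (Covariates; Statistical analysis; Abstract). Yearly outpatient visits and "history of pneumonia in 24-month before study start" are listed covariates. The final model takes significant variables, confounders and those judged clinically important. The Abstract names only age, sex and comorbidities.

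**The concern.** A recorded dose normally implies at least one visit to the centre. A blank field implies nothing: the person may be unvaccinated, may have been vaccinated elsewhere, or may be on the list without using the centre. The rule treats these people alike.

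Two mechanisms follow.

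- **Event-free person-time.** A registrant who has moved away without deregistering, or who uses care elsewhere, contributes up to 30 months in which an event may never reach the study's databases. Never-users of the centre bring this time into the comparison group only. That lowers the unvaccinated event rate and raises the hazard ratio.
- **Unrecorded doses.** A newcomer vaccinated elsewhere without a transferred record counts as unvaccinated, which pulls the hazard ratio toward 1.

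The study is sized to detect effectiveness of only 14% to 23%, so a modest distortion can hide an effect of the size it seeks.

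**Working it through.** **Inputs from the Rationale for sample size.** N = 27,000, coverage about 50% (13,500 per group), 30 months (2.5 years), two-sided 0.05. Rates per 1000 are 10 (CAP), 8 (AMI) and 12 (stroke). The last two carry no time unit and are taken as yearly. Target effectiveness (VE) is 20%, 23%, 18% and 14% (AMI/stroke combined).

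**Step 1: the plan's own power.** For CAP, the 30-month risks are 0.010 × 2.5 = 0.025 and 0.025 × 0.80 = 0.020. A two-proportion normal approximation with 13,500 per group gives 79.1%. The other endpoints, read the same way, give 81.8% (AMI), 77.7% (stroke) and 78.0% (combined). If the stated rates are overall rather than unvaccinated rates, stroke is 81.5% and combined 81.0%. The stated 80% is reproduced to rounding, and no error is raised there.

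**Step 2: event-free person-time.** Let gu and gv be the shares of unvaccinated and vaccinated person-time with no event capture. The document gives neither, so both are assumed.

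Observed HR = true HR × (1 − gv) / (1 − gu)

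CAP, true HR 0.80:

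| gu | gv | Observed HR | Observed VE | Crude power |
|---|---|---|---|---|
| 5% | 0 | 0.80/0.95 = 0.842 | 15.8% | 56% |
| 10% | 0 | 0.80/0.90 = 0.889 | 11.1% | 30% |
| 10% | 5% | 0.80 × 0.95/0.90 = 0.844 | 15.6% | 52% |
| 10% | 10% | 0.800 | 20.0% | 75% |
| 5% | 10% | 0.80 × 0.90/0.95 = 0.758 | 24.2% | 91% |

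With gu = 10% and gv = 0, a vaccine with no effect shows HR 1/0.90 = 1.11. Under the same assumption VE falls from 23% to 14.4% (AMI: 0.77/0.90 = 0.856), from 18% to 8.9% (stroke: 0.82/0.90 = 0.911) and from 14% to 4.4% (combined: 0.86/0.90 = 0.956). If half the events of that 10% are captured, CAP VE is 15.8%, since 0.80/(1 − 0.05) = 0.842.

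**Step 3: unrecorded doses alone.** Let m be the share of the comparison group that was in fact vaccinated (assumed).

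Observed HR = HR / (1 − m + m × HR)

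- m = 5%: 0.80/0.99 = 0.808, VE 19.2%.
- m = 10%: 0.80/0.98 = 0.816, VE 18.4%.
- True HR 1: no bias at any m.

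The event-free share therefore matters more than the misclassified doses.

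**The case against.** The strongest reply is that the error is not one-sided. Doses from the prior 10 years count, so someone vaccinated early in the programme who later stopped using the centre stays in the vaccinated group and adds event-free time there. Equal inactive shares cancel, and a larger share among vaccinees reverses the bias. This stands. A reader might infer that every inactive or newly arrived registrant falls in the comparison group, and the document does not support that. Truly unvaccinated newcomers are also classified correctly.

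Zero event capture is a worst case. AMI and stroke are hospital endpoints taken from discharge databases, so an admission to either reference hospital is found without any primary care use. Person-time is also censored when enrolment ends. Both points stand; they do not cover registrants who have moved away without deregistering or who are treated elsewhere.

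Three further readings go too far:

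- **Apparent harm.** With a true VE of 20%, the HR reaches 1 only when the event-free share is 20% (0.80/0.80) with none among vaccinees. Smaller shares attenuate the effect without reversing it.
- **Missing comorbidity codes as a downward bias.** If comorbidities are under-recorded in unvaccinated people whose events are captured, adjustment understates their baseline risk and raises VE.
- **A contradiction with the look-back windows.** The 24-month and 10-year windows define covariate and dose histories. They are not eligibility rules.

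Attendance is already a listed covariate and may remove part of the bias. The model-building rule does not guarantee its inclusion, however, and it cannot correct unrecorded doses.

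**Conclusion.** The concern holds in limited form. As written, the rules let never-users enter only the comparison group and misclassify newcomers whose earlier doses did not reach the record. A net downward bias is probable because doses are given at visits, but the document does not show that the inactive share is larger among the unvaccinated.

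The size is unknown. The reductions to 15.8% and 11.1% rest on assumed shares of 5% and 10%, no event capture, no inactive vaccinees and no adjustment. They show that small shares could matter against targets of 14% to 23%; they do not estimate what will happen.

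**What to change.** In Design, setting and study population and in Vaccination history, define an analysis set of people registered with a participating centre for at least 24 months before 1 January 2009 and with at least one recorded contact in that period. Apply it equally to both vaccination groups, so that it helps whichever way the imbalance runs. Report it with the all-registrant analysis, naming one as primary and the other as a pre-specified sensitivity analysis. In Statistical analysis, always include attendance in the adjusted models, with zero visits as a separate category. Report how many people the filter removes, by vaccination status.

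The cost is protocol wording and a filter on registration and visit data. The cohort shrinks slightly: if 10% of the comparison group is removed (an assumption), N = 12,150 + 13,500 = 25,650 and CAP power is about 77%, against 79.1% in the reproduction. The restricted estimate applies to users of the health service rather than to the general population over 60, which is why the all-registrant analysis stays. The 24 months do not recover unrecorded doses given earlier elsewhere, and a filter at study start does not catch people who leave later without deregistering.

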### Covariates

Covariates will be age, sex, frequency of attendance (number of outpatient visits per year), history of pneumonia in 24-month before study start, history of coronary artery disease, history of prior stroke, presence of major cardiovascular risk factors (hypertension, hypercholesterolaemia, smoking, diabetes mellitus or obesity), presence of major comorbidities (chronic heart disease, chronic pulmonary disease, severe liver disease, chronic nephropathy or cancer) and immunological status. Table 2 lists covariates and shows criteria used to measure and capture underlying conditions and comorbidities in the study cohort.

**Table 2 T2:** Definitions and criteria used to collect respiratory and cardiovascular risk factors and main comorbidities among cohort members in the CAPAMIS Study.*

UNDERLYING CONDITIONS	DEFINITIONS
**History of prior pneumonia**	Includes influenza-related pneumonia (J10.0 and J11.0), viral pneumonia (J12), pneumococcal pneumonia (J13), pneumonia due to Haemophillus influenzae (J14), bacterial pneumonia (J15), pneumonia due to other infectious organisms (J16), pneumonia in diseases classified elsewhere (J17) and pneumonia due to unspecified microorganisms (J18).

**History of coronary artery disease**	Includes angina (I20), acute myocardial infarction (I21), subsequent or recurrent myocardial infarction (I22) and chronic ischaemic heart disease (I25).

**History of stroke**	Includes haemorrhagic stroke (I60 to I62), cerebral infarction (I63) and stroke not specified as haemorrhage or infarction (I64); it does not include transient ischaemic attacks (code G45).

**Hypertension**	Defined as the presence of any code I10, I11, I12, I13 or I15.

**Hypercholesterolemia**	Defined as the presence of code E78.

**Diabetes mellitus**	Codes E10 to E14.

**Obesity**	Patients with registered code E66 (BMI>30%).

**Smoking**	Includes patients with current smoking (code F17 active at study start).

**Alcoholism**	Includes patients with code F10 active at study start.

**History of heart disease**	Includes congestive heart failure (I50), hypertensive heart disease (I11), cardiomyopathy (I42), cardiac dilatation or ventricular hypertrophy (I11.9 or I51.7) and coronary artery disease (I20, I21, I22 and I25).

**History of vascular ischaemia**	Besides coronary artery disease and stroke, it Includes atheroesclerosis (I70), acute arterial embolism or thrombosis (I74) and peripheric arterial disease or intermittent claudication (I73.9).

**Chronic pulmonary disease**	Includes chronic bronchitis or emphysema (J42 to J44) and asthma: (J45).

**Severe liver disease**	Includes chronic viral hepatitis (B18), alcoholic hepatitis (K70) and cirrhosis (K74).

**Severe nephropathy**	Includes nephrotic syndrome (N04 or N39.1), renal failure (N18, N19) and kidney dialysis (Y84.1) or transplantation.

**Immunocompromise**	Defined as the presence of any immunodeficiency (D80 to D84), AIDS (B20 to B24), anatomic or functional asplenia (D73.0 and Q89.0), cancer, severe nephropaty, or long-term corticosteroid therapy (20 mg/day of prednisone or equivalent).

* Data will be considered at the beginning of the study, and it will be defined according to the International Classification of Diseases 10th Revision (ICD-10) codes registered in the primary care clinical record of each cohort member at the start of the study.

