### Use of pneumococcal vaccine in the study area

In Catalonia, a region in the northeast of Spain with a population of seven million people, a publicly funded anti-pneumococcal vaccination programme for all individuals 65 years or older (with or without risk factors) and younger individuals with certain high-risk conditions (basically immunodeficiency, chronic heart or pulmonary disease, diabetes mellitus, severe liver disease or chronic nephropathy) began in October 1999. Further, it was extended for all people 60 years or older in 2002. Since then, a free PPV-23 has been offered when the patients came to the primary care services during the annual influenza vaccination campaigns or in any other visit throughout the year. Some years later, vaccination uptake reached approximately fifty percent,[31] and this provided an excellent opportunity to evaluate the vaccine's effects among the population. The potential effects of vaccination in preventing IPD and pneumonia have been analyzed in our reference population in two prior studies [32,33].

This project proposes a large population-based cohort study with the major aim of evaluating the clinical effectiveness of the PPV-23 against CAP as well as evaluating its potential role in cardiovascular prevention among the general population over 60 years.

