### Rationale for sample size

The annual incidence of CAP in older adults in the study area is estimated at approximately 10 per 1000 person-year based on prior population-based studies among elderly people in the same study area [34,35]. Incidences of AMI and stroke are estimated in 8 and 12 cases per 1000, respectively, in Spanish population [36,37]. Thus, considering a pneumococcal vaccine coverage of approximately 50%,[31] with a p = 0.05 (two-tailed) the size of the study cohort (N = 27,000 individuals followed during a 30-month period) has an statistical power of 80% to detect a posible vaccination effectiveness of 20% against CAP, a 23% against AMI, a 18% against stroke and a 14% against the combined end-point AMI/stroke.

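### The covariate set has no measure of dementia, non-stroke disabling neurological disease or functional dependence, so residual confounding of the CAP and all-cause death hazard ratios cannot be ruled out

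*Protocol article*

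**What the plan says.** The Covariates section fixes the adjustment set: age, sex, outpatient visits per year, pneumonia in the preceding 24 months, coronary disease, prior stroke, the main cardiovascular risk factors, and "presence of major comorbidities (chronic heart disease, chronic pulmonary disease, severe liver disease, chronic nephropathy or cancer) and immunological status". Table 2 defines the conditions by ICD-10 codes in the primary care record at study start, and adds alcoholism and vascular ischaemia. Under Vaccination history and Statistical analysis, influenza vaccination is re-evaluated yearly and modelled as time-varying.

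On access to the vaccine, the Background states that "a free PPV-23 has been offered when the patients came to the primary care services during the annual influenza vaccination campaigns". The sentence goes on to include any other visit during the year. On eligibility, "Exclusion criteria include residence in a long-term care facility"; the cohort is otherwise community-dwelling people aged 60 or over.

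CAP and death from any cause are both primary endpoints (Main outcomes and definitions). Vaccine effectiveness (VE) is one minus the hazard ratio, as a percentage. Final models adjust for significant variables, confounders and other baseline variables judged clinically important (Statistical analysis).

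**The concern.** Exposure here depends on contact with a primary care centre. Someone with dementia, advanced Parkinson's disease or severe dependence who lives at home may attend less, and may also have a higher risk of pneumonia and death. If both hold, dependent people are over-represented among the unvaccinated and the vaccine looks better than it is.

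No listed covariate measures this directly. Prior stroke covers one cause of disability. A low visit count mixes the very well with the house-bound. Influenza vaccination shares the access route and is a partial proxy, but it does not separate a dependent person from someone who declines vaccines. Excluding care-home residents removes many of the most dependent, but not those cared for at home.

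Because VE is read straight from the hazard ratio, whatever confounding remains passes directly into the headline figure. The sample-size section targets a VE of only 20% for CAP, so a distortion of several points matters.

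**Working it through.** **1. The plan's own figure.** The section Rationale for sample size gives "N = 27,000 individuals followed during a 30-month period", a CAP incidence "estimated at approximately 10 per 1000 person-year", about 50% coverage and two-sided 0.05, and says the cohort "has an statistical power of 80% to detect a posible vaccination effectiveness of 20% against CAP".

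- Incidence read as the unvaccinated rate: risks 0.010 × 2.5 = 0.025 and 0.025 × 0.80 = 0.020, with 13,500 per group. SE = √[(0.025 × 0.975 + 0.020 × 0.980)/13,500] = 0.00180. Power = Φ(0.005/0.00180 − 1.96) = 79.1%.
- Incidence read as the overall rate: events = 27,000 × 2.5 × 0.010 = 675. SE of log HR = √(4/675) = 0.077. Power = Φ(0.223/0.077 − 1.96) = 82.6%.

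Both bracket the stated 80%. On the first reading, the VE detectable with 80% power is 20.3% (CAP), 22.6% (AMI), 18.5% (stroke) and 14.4% (AMI/stroke), against the stated 20, 23, 18 and 14. The power statement stands. It serves here only to supply the 675 CAP events and the target VE.

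**2. What the covariate set contains.** Checking the Covariates section and Table 2 item by item: prior stroke (I60 to I64) is the only neurological item. There is no code for dementia, Parkinson's disease, multiple sclerosis or paralysis, and no item for dependence or home care. The rule admitting other clinically important baseline variables does not supply one, because none is listed as collected.

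**3. Possible size of the bias.** The documents give no prevalence of dependence, no uptake by dependence and no associated risk, so every input in this step is an assumption. With prevalence p₁ in the vaccinated and p₀ in the unvaccinated, and hazard ratio h for dependence, a null vaccine shows approximately

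HR = [1 + p₁(h − 1)] / [1 + p₀(h − 1)], and apparent VE = 1 − HR.

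| p₁ (vaccinated) | p₀ (unvaccinated) | h = 2 | h = 3 | h = 4 |
|---|---|---|---|---|
| 6% | 10% | 1.06/1.10 = 0.964; VE 3.6% | 1.12/1.20 = 0.933; VE 6.7% | 1.18/1.30 = 0.908; VE 9.2% |
| 4% | 6% | 1.04/1.06 = 0.981; VE 1.9% | 1.08/1.12 = 0.964; VE 3.6% | 1.12/1.18 = 0.949; VE 5.1% |
| 10% | 6% | 1.10/1.06 = 1.038; VE −3.8% | 1.20/1.12 = 1.071; VE −7.1% | 1.30/1.18 = 1.102; VE −10.2% |

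The last row swaps the prevalences of the first, and the sign reverses. In the first row, a true VE of 20% would read as 1 − 0.80 × 0.964 = 22.9% up to 1 − 0.80 × 0.908 = 27.4%.

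**4. Chance of a false finding for CAP.** With SE 0.077 and the first row's assumptions, the probability that a null vaccine reaches p < 0.05 in its favour is Φ(|ln 0.964|/0.077 − 1.96) ≈ 7% at h = 2 and Φ(|ln 0.908|/0.077 − 1.96) ≈ 24% at h = 4. The nominal figure is 2.5%.

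These are values before any adjustment. Age, prior stroke, prior pneumonia, attendance and influenza vaccination would probably absorb part of the imbalance.

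**The case against.** The strongest case against is that the mechanism is not in the documents. Nothing says that dependent people are vaccinated less. The offer extends to any visit, and frequent contact could raise uptake among the ill. Timing weakens the link further: the programme began in 1999, was widened in 2002, and doses from the previous 10 years count. A person dependent in January 2009 may have been vaccinated years earlier while mobile. Several listed covariates are partial proxies, influenza vaccination above all, because it shares the access route. Finally, the article condenses a fuller protocol, and one more desirable confounder can be named for almost any cohort.

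Most of this stands, and it limits the point. A reader might infer that dependent members are in fact unvaccinated and that a spurious benefit will follow. The documents support neither the premise nor a certain direction. A reader might also infer that neurological disease is wholly absent; prior stroke is there. Nor is there any calculation to show that death would be affected more than CAP.

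What does not stand is that the gap is only missing detail. The article states the covariate list and its code definitions explicitly. Uncertainty about the direction of the bias is a reason to measure dependence.

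**Conclusion.** The point holds as a gap in the adjustment set, not as a demonstrated bias. Dementia, non-stroke disabling neurological disease and functional dependence are not among the listed covariates, and the model rule cannot adjust for what is not collected. Residual confounding of the CAP and all-cause death hazard ratios, plausibly toward apparent protection, therefore cannot be ruled out.

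Any size rests wholly on assumed prevalences and hazard ratios. It is a few points of VE under moderate assumptions (1.9% to 9.2% across the two scenarios with more dependence among the unvaccinated), less once correlated covariates are in the model, and of opposite sign if dependent people are vaccinated more often. This is a worthwhile, inexpensive improvement; it does not invalidate the design or the power statement.

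**What to change.** Add to Table 2, from the same baseline ICD-10 extraction:

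- dementia (F00–F03, G30);
- Parkinson's disease or other disabling neurological disease (G20, G35, G81–G83);
- an indicator of home care or home visits, if the primary care record holds one. The documents do not say whether it does.

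Keep these terms in the models regardless of statistical significance. Report the CAP and all-cause death hazard ratios with and without them, so that readers can see whether the concern has substance and in which direction.

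The cost is a few more codes in a query already being run and a few model terms, which the expected 675 CAP events can carry. The paralysis codes will partly overlap with prior stroke, so collinearity should be looked at, as the plan already intends. The main drawback is incomplete coding of dementia and dependence, which makes the adjustment partial; a small change in the hazard ratio would not prove that confounding is absent.
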